## Appendix 5A: TaMoVac I Assessment of Understanding (English)

Please read each question and answer whether the statement is True or False.

| True                     | False                    |     |                                                                                                                                                       |
|--------------------------|--------------------------|-----|-------------------------------------------------------------------------------------------------------------------------------------------------------|
|  |  | 1.  | Volunteers in this vaccine study will be protected against HIV and never have to worry about becoming HIV infected.                                   |
|  |  | 2.  | The vaccine in this study will give you HIV.                                                                                                          |
|  |  | 3.  | A purpose of this study is to see whether the vaccine is safe.                                                                                        |
|  |  | 4.  | If you enter this study, you may receive an inactive substance called a placebo instead of the vaccine.                                               |
|  |  | 5.  | This vaccine has been shown to be safe in pregnant women, and a woman may become pregnant during this study if she wishes.                            |
|  |  | 6.  | This study will require you to come to the clinic multiple times for visits and blood draws over the next 17 months.                                  |
|  |  | 7.  | Volunteers in this vaccine study can get infected with HIV if they have unprotected sex or if they share sharp instruments.                           |
|  |  | 8.  | You may take other experimental (test) products while you are taking part in this study.                                                              |
|  |  | 9.  | You may withdraw from the study at any time if you choose or your participation may be stopped if the study team decides it is in your best interest. |
|  |  | 10. | As a result of the immunization, you may test positive for HIV. However, by using other tests we can determine that you are not infected with HIV.    |
|  |  | 11. | All components of this vaccine regimen have been previously used in human volunteers.                                                                 |
|  |  | 12. | The vaccine used in this study has copied parts of the HIV virus.                                                                                     |
|  |  | 13. | I can participate in other studies investigating new drugs or vaccines during the same time.                                                          |
|  |  | 14. | This study tests if this HIV vaccine can protect individuals from acquiring HIV infection.                                                            |

|                          |                          |     |                                                                                                                                                                            |
|--------------------------|--------------------------|-----|----------------------------------------------------------------------------------------------------------------------------------------------------------------------------|
|  |  | 15. | The conduct of the study is overseen by others including the regulatory authorities in Tanzania                                                                            |
|  |  | 16. | The multiple blood samples taken from me could be subjected to genetic tests                                                                                               |
|  |  | 17. | By participating in this study, I am not allowed to father a child or become pregnant during the study period and 6 months after receiving the last vaccine dose           |
|  |  | 18. | If I voluntarily decide to withdraw from the study, I will continue to receive care at the Muhimbili National Hospital or the Mbeya Referral Hospital in case of sickness. |
|  |  | 19. | The nurse who gives me the vaccine knows whether I am getting vaccine or placebo                                                                                    |

**Test repetition number: 1 2 3**

**Number and % or correct answers:** /19, %

## Appendix 5B: TaMoVac I Assessment of Understanding (Swahili)

### TaMoVac I-MTIHANI WA KUPIMA UFAHAMU (TOU)

**Tafadhali soma kila swali na kujibu maelezo yanayofuata kama Kweli (K) au Si kweli (S).**

| Kweli                    | Si kweli                 |     |                                                                                                                                                                                          |
|--------------------------|--------------------------|-----|------------------------------------------------------------------------------------------------------------------------------------------------------------------------------------------|
|  |  | 1.  | Washiriki wa utafiti huu watapata kinga dhidi ya VVU na hawatakuwa na wasiwasi wa kupata maambukizi.                                                                                     |
|  |  | 2.  | Chanjo katika utafiti huu itakupa maambukizi ya VVU                                                                                                                                      |
|  |  | 3.  | Lengo la utafiti huu ni kutafiti kama chanjo hii ni salama                                                                                                                               |
|  |  | 4.  | Kama utajiunga na utafiti huu, unaweza kupata mchanganyiko usiofanya kazi (placebo) badala ya chanjo.                                                                                    |
|  |  | 5.  | Chanjo hii imethibitika kuwa ni salama kwa wanawake wajawazito na mama anaweza kushika mimba wakati utafiti ukiendelea akipenda                                                          |
|  |  | 6.  | Utahitajika ufike kliniki mara nyingi kwa ajili ya mahudhurio na vipimo vya damu kwa kipindi cha miezi 17                                                                                |
|  |  | 7.  | Washiriki wanaweza kupata maambukizi ya VVU kama watafanya ngono bila kinga au kushirikiana vyombo vyenye makali.                                                                        |
|  |  | 8.  | Unaweza kutumia chanjo au dawa nyingine za majaribio wakati ukishiriki katika utafiti huu                                                                                                |
|  |  | 9.  | Unaweza kuacha kushiriki muda wowote kama ukiamua au kusimamishwa kama ikionekana kuwa kufanya hivyo ni kwa faida yako.                                                                  |
|  |  | 10. | Baada ya kupata chanjo, unaweza kuonekana kuwa umeathirika kwa vipimo vya kawaida kama ELISA lakini kwa kutumia vipimo vingine inaweza kuthibitishwa kwamba wewe huna maambukizi ya VVU. |
|  |  | 11. | Viasili mchanganyiko vyote vya chanjo hii vimekuwa vikitumika huko nyuma katika binadamu wa kujitolea.                                                                                   |
|  |  | 12. | Chanjo hii katika utafiti huu ina viasili vitokanavyo na sehemu za kirusi cha Ukimwi.                                                                                                    |
|  |  | 13. | Naweza kushiriki katika tafiti zingine za kugundua dawa mpya au chanjo wakati mmoja.                                                                                                     |
|  |  | 14. | Utafiti huu unapima kama chanjo hii ya VVU inaweza kuzuia watu wasipate maambukizi ya VVU.                                                                                               |

|                          |                          |     |                                                                                                                                                         |
|--------------------------|--------------------------|-----|---------------------------------------------------------------------------------------------------------------------------------------------------------|
|  |  | 15. | Utafiti unavyoendeshwa chini ya uangalizi wa watu wengine ikiwemo na mamlaka za maadili za utafiti Tanzania,                                            |
|  |  | 16. | Damu zinazochukuliwa toka kwangu zitatumika kupima viasili vilivyomo.                                                                                   |
|  |  | 17. | Wakati wa kushiriki katika utafiti huu,siruhusiwi kuzaa mtoto au kupata ujauzito na miezi 6 baada ya kupata chanjo ya mwisho.                           |
|  |  | 18. | Kama nitajiondoa kutoka katika utafiti,nitaendelea kupata huduma toka hospitali ya taifa Muhimbili au hospitali ya rufaa ya Mbeya kama nitakuwa naumwa. |
|  |  | 19. | Muuguzi anayenipa chanjo huwa anafahamu kama ananipa chanjo harisi au isio harisi (placebo).                                                            |

Kurudia kufanya Mtihani huu wa kupima ufahamu ni mara 1,2,3

Idadi ya maswali aliojibu na asilimia yake au majibu sahihi: /19, %

## Appendix 6A: TaMoVac I Risk Assessment of Volunteers (English)

We will ask you about your sexual experience. You do not have to answer any questions that make you feel uncomfortable however; this may affect your eligibility and opportunity to participate in this trial. All your answers will be treated confidentially. No one will be allowed to disclose our answers outside our research group.

1. Have you ever had sexual intercourse?
  - a. ☐ Yes
  - b. ☐ Never had (*jump to questions 7, 8, 9 and 10*)
2. How many sexual partners have you had during the past six months?
  - a. ☐ ≤ Two (2)
  - b. ☐ More than Two
3. Are you in a relationship with an HIV infected partner?
  - a. ☐ Yes
  - b. ☐ No
  - c. ☐ I don't know
4. Among the people you have had sex with, are there any individuals who you knew or suspected were HIV positive in the past 6 months?
  - a. ☐ Yes (Knew or Suspected)
  - b. ☐ No
5. In the past 6 months, how often have you had sexual intercourse with prostitutes or exchanged sex for money, goods or services?
  - a. ☐ Have NOT had sexual intercourse with prostitutes in the past 6 months
  - b. ☐ Have NOT exchanged sex for money, goods or serviced in the past 6 months
  - c. ☐ Have had sexual intercourse with prostitutes in the past 6 months
  - d. ☐ Have exchanged sex for money, goods or serviced in the past 6 months
6. During the past 6 months, have you used condoms during sexual intercourse with casual partners?
  - a. ☐ Always
  - b. ☐ Sometimes
  - c. ☐ Seldom or Never
7. In the past 6 months, have you been diagnosed with a sexually transmitted disease?
  - a. ☐ Yes
  - b. ☐ No
8. In the past 6 months, have you had any of the following symptoms?
  - a. ☐ Genital sores
  - b. ☐ Discharge from vagina with itching or burning
  - c. ☐ Pus discharge from penis
  - d. ☐ Frequent, difficult, or painful urination
  - e. ☐ None of the above

9. Are you regular drinking alcohol defined as >21 units per week (male), >14 units per week (female) → 1 units = 1 beer or 1 glass of wine or measure of strong alcohol.

- a. ☐ Yes
- b. ☐ No

10. Have you ever used intravenous recreational drugs?

- a. ☐ Yes
- b. ☐ No

The use of this assessment tool is designed to facilitate a discussion with the patient and inform clinical judgment about volunteer risk. It is not a validated instrument and seeks to briefly identify high-risk behaviors which would be grounds for excluding a volunteer.

## Appendix 6B: TaMoVac I Risk Assessment of Volunteers (Swahili)

### KUPIMA UWEZEKANO WA MTU KUWA KATIKA HATARI YA KUPATA MAAMBUKIZO YA VVU

Tutakuuliza kuhusu historia yako ya kujamiana. Huwezi kujibu maswali yote ambayo hutajisikia vizuri kuyajibu japo itaathiri vigezo vyako na nafasi yako ya kushiriki katika utafiti wa majaribio haya. Majibu yako yote yatakuwa siri. Hakuna atakayeruhusiwa kutoa taarifa zako za siri nje ya kundi la utafiti.

1. Umewahi kujamiana?
  - a. ☐ Ndiyo
  - b. ☐ Hapana Sijawahi [nenda swali la 7,8, 9 na 10]
2. Umekuwa na wapenzi wangapi kipindi cha miezi sita iliyopita?
  - a. ☐ Wawili au mmoja
  - b. ☐ Zaidi ya wawili
3. Je una mahusiano ya kimapenzi na mtu mwenye Virusi Vya Ukimwi (VVU)?
  - a. ☐ Ndiyo
  - b. ☐ Hapana
  - c. ☐ Sifahamu
4. Katika kipindi cha miezi iliyopita, kati ya wale uliofanya nao mapenzi, kuna ambao unafahamu au unawahisi wana maambukizi ya VVU?
  - a. ☐ Ndiyo (Kufahamu au Kuhisi)
  - b. ☐ Hapana
5. Katika kipindi cha miezi sita iliyopita, ni mara ngapi umefanya mapenzi na wanawake/wanaume wanaojiuza (changudoa) au kufanya mapenzi kwa sababu ya kupata pesa, vitu au huduma?
  - a. ☐ Sijafanya mapenzi na watu wanaojiuza (changudoa) ndani ya miezi sita (6) iliyopita
  - b. ☐ Sijafanya mapenzi kwa ajili ya kupata pesa, vitu au huduma katika miezi sita (6) iliyopita
  - c. ☐ Nimefanya mapenzi na watu wanaojiuza (changudoa) ndani ya miezi sita (6) iliyopita
  - d. ☐ Nimefanya mapenzi ili kupata pesa, vitu au huduma katika miezi sita (6) iliyopita
6. Katika miezi sita (6) iliyopita, umewahi kutumia kondomu wakati wa kujamiana na mpenzi/wapenzi wako?
  - a. ☐ Mara zote
  - b. ☐ Mara nyingine
  - c. ☐ Mara Chache au Sijawahi
7. Katika miezi sita (6) iliyopita, umewahi kupata magonjwa ya zinaa?
  - a. ☐ Ndiyo
  - b. ☐ Hapana

8. Ndani ya miezi sita (6) iliyopita, je umepata moja ya dalili zifuatazo?
- a. ☐ Vidonda sehemu za siri
  - b. ☐ Uchafu kutoka ukeni ukiambatana na kuwashwa/maumivu
  - c. ☐ Usaha kutoka kwenye uume
  - d. ☐ Maumivu/shida wakati wa kukojoa na kukojoa mara kwa mara
  - e. ☐ Hakuna dalili
9. Una kawaida ya kunywa pombe zaidi ya 21 kwa wiki? (pombe = chupa ya bia au glasi ya waini au pombe kali)
- a. ☐ Ndiyo
  - b. ☐ Hapana
10. Umewahi tumia dawa za kulevya?
- a. ☐ Ndiyo
  - b. ☐ Hapana

Maswali haya katika kipengele hiki yamelenga kurahisisha majadiliano na mshiriki ili kuweza kuamua kama mshiriki yupo katika hatari kubwa ya kupata maambukizi ya VVU. Maswali haya si kipimo halisi cha uwezekano wa mshiriki kupata maambukizi ya VVU bali yanadhamiria kutoa taarifa ambazo zinaweza kumfanya mtu asishiriki katika utafiti.

## Appendix 7: TaMoVac I Project - HIV Testing Algorithm

[figure not shown]

\* First quantitative HIV-RNA-PCR with detection limit <400 copies/ml, if negative the ultra-sensitive HIV-RNA-PCR with detection limit <50 copies/ml will be performed for confirmation.

# HIV test results during the study will be reported to the clinic only as “infected” or “not infected” for the purpose of not unblinding due to potentially “false positive” test results in vaccine recipients.

## Appendix 8A: TaMoVac I Diary Card (English)

*(Enter Site Logo Here)*

### TaMoVac I Participant Diary Card

Site Name and Location

Version 1.0

18 September 2008

Study ID

Vaccination #

Site Address

Phone: *Site Phone Number*

After Work Hours: *Site Phone Number*

FAX: *Site FAX Number*

[figure not shown]

### Symptoms Severity Scale

None

**Mild**= minimal symptoms; cause minimal or no interference with work, school, or self care activities.

**Moderate**=notable symptoms; required modification in activity; did not result in loss of work or cancellation of social activities

**Severe** = incapacitating symptoms; requiring bed rest and/or resulted in loss of work or cancellation of social activities.

For any Problems Call *Site Name* at  
(   ) *Site Phone Number* OR (   ) *Site Phone Number*

### Injection Site Severity Scale

[figure not shown]

None

[figure not shown]

**Mild**= minimal symptoms; cause minimal or no interference with work, school, or self care activities.

[figure not shown]

**Moderate**=notable symptoms; required modification in activity; did not result in loss of work or cancellation of social activities

[figure not shown]

**Severe** = incapacitating symptoms; requiring bed rest and/or resulted in loss of work or cancellation of social activities.

## Evening of Vaccination

Date: \_\_\_\_\_

Temp: \_\_\_\_\_ Time Taken: \_\_\_\_\_

If you have a fever and wish to take your temperature during the night, record your additional temperature:

Temp: \_\_\_\_\_ Time Taken: \_\_\_\_\_ Temp: \_\_\_\_\_ Time Taken: \_\_\_\_\_

Are you taking any medication? Yes No

Specify: \_\_\_\_\_

Please use the symptom scale at the bottom of the page

| General Symptoms | None | Mild | Moderate | Severe |
|------------------|------|------|----------|--------|
| Malaise/ Fatigue |      |      |          |        |
| Chills           |      |      |          |        |
| Aching Joints    |      |      |          |        |
| Muscle Aches     |      |      |          |        |
| Headache         |      |      |          |        |
| Nausea           |      |      |          |        |
| Vomiting         |      |      |          |        |

| Injection Site Symptoms | None                   | Mild | Moderate | Severe | None                   | Mild | Moderate | Severe |
|-------------------------|------------------------|------|----------|--------|------------------------|------|----------|--------|
| Local Pain              |                        |      |          |        |                        |      |          |        |
| Local Itching           |                        |      |          |        |                        |      |          |        |
| Warmth                  |                        |      |          |        |                        |      |          |        |
| Swelling (in cm)        | ____. __X _____. __ cm |      |          |        | ____. __X _____. __ cm |      |          |        |
| Redness (in cm)         | ____. __X _____. __ cm |      |          |        | ____. __X _____. __ cm |      |          |        |
| Induration (in cm)      | ____. __X _____. __ cm |      |          |        | ____. __X _____. __ cm |      |          |        |
| Clear blister (in cm)   | ____. __X _____. __ cm |      |          |        | ____. __X _____. __ cm |      |          |        |
| Blood blister (in cm)   | ____. __X _____. __ cm |      |          |        | ____. __X _____. __ cm |      |          |        |
| Papule (in cm)          | ____. __X _____. __ cm |      |          |        | ____. __X _____. __ cm |      |          |        |

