## **11 ENDPOINTS**

### **11.1 Safety**

The safety of immunization with the seven DNA plasmids carrying HIV-1 genes and the MVA will be assessed by clinical features as well as standard biochemical and hematological laboratory tests. Any worsening of the severity grade will be considered for causality with the vaccine.

Safety endpoints: Adverse events will be assessed using a standard format for soliciting local and systemic reactogenicity to the vaccine and collection of unsolicited adverse events. Solicited reactogenicity will be evaluated for 7 days following each vaccination. All other AE will be collected from the time of first injection until 3 months after the last injection.

The primary safety parameters will be graded according to the DAIDS Table for Clinical and Lab Criteria for Definitions (*see Appendix 9*) and are:

1. Local adverse event Grade 3 or above (pain, cutaneous reactions including indurations)
2. Systemic adverse event Grade 3 or above (fever, chills, headache, nausea, malaise, myalgia, and arthralgia)

3. Other clinical and laboratory adverse event Grade 3 or above confirmed at examination or on repeat testing respectively

The relationship to the vaccine should be evaluated as:

- 1= not related
- 2= probably not related
- 3= possibly related
- 4= probably related
- 5= definitely related

Tests for possible toxicity due to vaccination will include: Liver function tests, renal function tests and complete blood count and differential with platelets. Any event attributable to vaccine leading to discontinuation of the immunization regimen must be documented.

Data on local and systemic events listed above will be solicited with specific questions or using a diary card for a minimum of 7 days following each immunization. Data on other clinical events and laboratory events will be collected with an open question at each visit and through routine scheduled investigations respectively.

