## 12 SAFETY AND IMMUNOGENICITY ASSESSMENTS

### 12.1 Safety assessment

Local and systemic assessments whether normal or abnormal will be recorded starting from 30 minutes up to 4 weeks after immunization in the following intervals: 30 minutes as direct observation after immunization, at the evening of the vaccination day and at days 1-7 as recorded by diary cards by the participants with clinic or home visit if indicated, plus follow-up safety visits 2 weeks and 4 weeks after each immunization. While study personnel will use the vaccine/reaction form (**CRF 10-I**) to record all local and systemic events at the clinic, participants will use diary cards at home for the same. On the Adverse Events Form (**CRF 6-I**) all medical events throughout the entire study period will be reported, excluding those local or systemic reactions indicated on the Vaccine/Reaction Form (**CRF 10-I**) during the first 7 days post vaccination. The study site will contact participants at the first day after vaccination for an adverse events/reaction interview. Participants will be instructed to call or report to the specified study personnel immediately if any unusual or severe sign or symptom appears after immunization. Participants with suspected grade 3 or above events should be seen in the clinic at the time of maximal symptoms, if possible, and will be followed up clinically until resolution of symptoms.

An adverse event is any undesired, noxious or pathological change in a participant as indicated by physical signs, symptoms, and/or laboratory changes that occurs following administration of one of the vaccines, whether or not considered vaccine related. This definition includes intercurrent illnesses or injuries, and exacerbation of pre-existing conditions.

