#### **12.1.1 Local adverse events**

Pain at the injection site will be graded by the volunteer according to the criteria in the DAIDS Table for Clinical and Lab Criteria for Definitions (**see Appendix 9**) as mild (1) moderate (2), severe (3) or serious/life threatening (4) and recorded in the appropriate case record form. In the diary card grading will refer only to mild (1) moderate (2) and severe (3) as the distinction between severe and serious should be made in association with the medical officer after having reported to the clinic once the volunteer has left clinic. Swelling, redness and indurations will be recorded as the maximum diameter as well as the presence of any itching or other discomfort and any medication taken for relief of symptoms. Blistering (vesiculation) or ulceration will be graded according to size, depth, time to healing and character of blisters (blood-filled).

Clinical staff will complete the case record form following each immunization. In the event that there are two observations on the same day, those confirmed at a visit will take precedence over diary card observations in the analysis. Study personnel should verify all grade 3 or 4 events.

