| Injection site pain (pain without touching)
Or
Tenderness (pain when area is touched) | Pain/tenderness causing no or minimal limitation of use of limb                                                                                    | Pain/tenderness limiting use of limb OR Pain/tenderness causing greater than minimal interference with usual social & functional activities | Pain/tenderness causing inability to perform usual social & functional activities                                                                                                                       | Pain/tenderness causing inability to perform basic self-care function OR Hospitalization (other than emergency room visit) indicated for management of pain/tenderness |
| Injection site reaction (localized)                                                         |                                                                                                                                                    |                                                                                                                                             |                                                                                                                                                                                                         |                                                                                                                                                                        |
| Adult > 15 years                                                                  | Erythema OR Induration of 5x5 cm – 9x9 cm (or 25 cm  – 81cm  )                                                             | Erythema OR Induration OR Edema > 9 cm any diameter (or > 81 cm  )                                                              | Ulceration OR Secondary infection OR Phlebitis OR Sterile abscess OR Drainage                                                                                                                           | Necrosis (involving dermis and deeper tissue)                                                                                                                          |

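### The diary card has no row for any of the adult Grade 3 signs of a local skin reaction, although the protocol presents local Grade 3 skin events as solicited for 7 days

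*Protocol*

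**What the plan says.** Section 11.1 lists as the first primary safety parameter "Local adverse event Grade 3 or above (pain, cutaneous reactions including indurations", graded by the DAIDS table in Appendix 9. It states that data on these local events "will be solicited with specific questions or using a diary card for a minimum of 7 days following each immunization". Section 12.1 says staff use CRF 10-I for local and systemic events at the clinic and that "participants will use diary cards at home for the same". Section 12.1.1 adds: "Blistering (vesiculation) or ulceration will be graded according to size, depth, time to healing and character of blisters (blood-filled".

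The diary in Appendix 8A carries nine injection-site rows on the evening page and on each of Days 1 to 7: pain, itching, warmth, swelling, redness, induration, clear blister ("Clear blister (in cm"), blood blister and papule. The daily pages of the Swahili card (Appendix 8B) have the same nine.

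For a localized injection-site reaction in adults, Appendix 9 gives Grade 2 as "Erythema OR Induration OR Edema > 9 cm any diameter" (or the equivalent area), Grade 3 as "Ulceration OR Secondary infection OR Phlebitis OR Sterile abscess OR Drainage" and Grade 4 as "Necrosis (involving dermis and deeper tissue".

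**The concern.** The primary parameter concerns Grade 3 and above. If the form used at home asks about none of the signs that define Grade 3 on the local skin line, the skin part of that parameter is collected mainly by spontaneous report or later recall, while the protocol describes it as solicited. An ulcer or discharging site that appears and heals before the next visit is the event most likely to be missed. This also touches the comparison of two against five intradermal injections in section 20.1, which covers events within 7 days.

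**Working it through.** No sample size, power or alpha figure enters here. The check sets the form against the grading table.

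**1. From diary row to adult grading line (Appendix 9).**

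| Diary row | Where it is graded |
|---|---|
| Pain | Injection-site pain line; can reach Grade 3 |
| Swelling, redness, induration | Localized reaction line; by size alone it stops at Grade 2 |
| Local itching | Injection pruritus line; Grade 3 there needs generalized itching, which the row does not ask for |
| Warmth, clear blister, blood blister, papule | No injection-site line of their own |

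**2. From grading criterion to diary row.** Ulceration: none. Secondary infection: none. Phlebitis: none. Sterile abscess: none. Drainage: none. That is 0 of 5 for Grade 3. Necrosis has no row either, so 0 of 1 for Grade 4. No page in either language, the stop-date page included, has such a row or an 'other' row.

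**3. Inside section 12.1.1.** Blistering and ulceration stand in one sentence as events to be graded. Blistering has two diary rows and ulceration has none.

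**4. Scheduled contacts.** These are 30 minutes after injection, a brief interview on day 1 whose questions are not given (section 9.3), and a follow-up visit at 14 days plus or minus 3 (Appendix 1). The visit therefore falls between day 14 − 3 = 11 and day 14 + 3 = 17. From day 2 to at least day 10 no staff contact is scheduled, and the diary (to day 7) is the only scheduled record of local signs.

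**5. Exposure.** Intradermal vaccine sites: groups IA and IIA, 72 × 2 × 3 = 432; group IIIA, 36 × 5 × 3 = 540; together 972. MVA injections: 108 × 2 = 216. These counts show how many sites the form has to cover. They say nothing about how often the signs occur.

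**The case against.** The other side has a good case on consequences.

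- **Section 11.1 allows specific questions or a diary.** It does not require the card to carry every criterion. Section 12.1.1 does not assign ulceration to the diary, and grading by depth and time to healing is clinicians' work. Secondary infection, phlebitis and sterile abscess are diagnoses that a volunteer should not be asked to make.
- **Other routes exist.** Volunteers are asked to contact the site for suspected Grade 2 or more (section 9.3) and at once for anything unusual or severe (section 12.1). A 24-hour number is given. At the two-week visit a medical officer goes through the diary and assesses medical status (section 8.4). Clinic or home visits are possible in the first week if indicated.
- **The events would be analysed once reported.** The two-versus-five comparison in section 20.1 includes unsolicited events within 7 days, section 12.1.3 records start and end dates, and the third primary parameter in section 11.1 takes other Grade 3 events confirmed at examination.
- **CRF 10-I is not shown.** It may have a field for ulceration.

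Most of this stands and limits the consequence. It does not remove the mismatch. A sore or a discharge is as visible to a lay person as the blisters the card already asks about. The protocol sets out no specific questions for days 2 to 10. The severity scale printed on each daily page for the injection site is worded in pain, tenderness and use of the arm, so a painless ulcer gives the volunteer no printed cue to call. Collection by call or open question is also not the solicited collection that section 11.1 describes.

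**Conclusion.** The mismatch is established from the protocol alone: none of the five adult Grade 3 criteria for a localized injection-site reaction has a diary row. These signs rest first on volunteer-initiated calls, then on diary review, examination or an open question, and some that heal before the visit may be under-recorded. This calls for a cheap improvement to the form. It is not a flaw that invalidates the safety analysis.

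Two stronger readings are tempting and are not supported.

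- A reader might infer that pain is the only diary row able to reach Grade 3. Appendix 9 has a general row for clinical events not listed elsewhere, and section 14.1 gives the same rule. Warmth or a blister that stops usual activities could be graded 3 that way.
- A reader might infer that Grade 3 skin events are lost, or that the primary count is biased low by a known amount. They can still be reported and analysed, and the documents give neither an event rate nor a capture rate. The size of any under-capture cannot be estimated.

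The verdict assumes that the day-1 interview and CRF 10-I, whose contents are not shown, contain no equivalent home question for days 2 to 7.

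**What to change.** Add two observable items per arm to the evening page, to Days 1 to 7 and to the stop-date page, in English and Swahili: 'open sore/ulcer (cm)' and 'pus or fluid from the site (yes/no)'. Put the same two items on CRF 10-I if it lacks them. Leave the diagnosis of secondary infection, phlebitis or abscess to study staff; the two rows are prompts and are not meant to reproduce all five criteria. Sections 11.1, 12.1 and 12.1.1, Appendix 9 and the card would then agree on how these events are collected.

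The cost is a slightly longer card and one form revision in two languages. No extra visits or staff are needed, and no clinical rule changes.
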